**Fig. 3 Fig3:**
[figure not shown]
Fitness Qigong eight-dan jin selection movements

#### Control group (CG)

Patients do not undergo any systematic exercise rehabilitation and only undergo a routine medication programme.

### Study results

#### Basic features

##### Lung function

Clinicians will use the hospital respiratory spirometer (Germany JAEGER-MasterScreen) to measure FEV1 (forced expiratory volume in 1 s), FVC (forced vital capacity), FEV1% predicted, FEV1/FVC ratio, MIP (maximum inspiratory pressure), MEP (maximum expiratory pressure), DLco (diffusing capacity of the lung for carbon monoxide), and DLco/VA in COPD patients. The variability characteristics of blood oxygen saturation (SpO2) and other relevant indicators measured by nail oximetry in humans(BERRY® BM1000F). Blood gas indicators such as oxygen saturation (SaO2) and partial pressure of oxygen (PaO2) were measured using a blood gas system (Siemens-RAPIDLab® 348EX) to assess blood gas indicators before and after the intervention, thereby assessing respiratory muscle strength, cardiopulmonary endurance and other functions in COPD patients [31, 32].

##### Respiratory distress symptoms

The subjective severity of the subject’s dyspnoea will be measured using the modified Medical Research Council Dyspnoea Scale (mMRC), the St. George’s Respiratory Questionnaire (SGRQ). The mMRC is a 5-point scale (0–4), with higher scores indicating worse dyspnoea. The SGRQ is a disease-specific questionnaire consisting of three domains (dyspnoea, impact and activity). Each score ranges from 0 to 100 (0 = no impairment), with higher scores indicating severe respiratory symptoms.

### Main results

#### Prefrontal cortex tissue oxygen saturation index (TSI)

Monitoring changes in dorsolateral prefrontal cortex (PFC) oxyhemoglobin concentration by fNIRS at all times during a cognitive task. fNIRS is a powerful tool for the non-invasive study of task-evoked brain activity, allowing real-time monitoring of changes in the concentration of oxyhemoglobin content on the prefrontal cortex during the task [33]. The frontal cortex tissue oxygen saturation index (TSI) is calculated as the ratio of oxy-Hb to the percentage of Total-Hb and reflects the balance between oxygen delivery and utilisation. In the brain, TSI is used as a proxy for tissue oxygenation. Neural activity triggers local changes in cerebral haemodynamics, which induce enhanced blood flow to activated brain regions (neurovascular coupling) [34–36]. It mainly proceeds due to the local oxygen supply being greater than its consumption and therefore higher concentrations of oxyHb and reduced concentrations of deoxyHb are observed in the activated brain regions.

For the measurement of the TSI, This study was designed to use a single-task walking test in two contexts. Also record the step frequency, step speed and walking time during the period. The first scenario was a single-task walk at a general pace (6 round trips on a 5-m trail analysis system for a total of 30 m). The general speed of the stride is based on the speed of walking at home. The second scenario is a fast walking single-task walk (6 round trips on a 5-m trail analysis system for a total of 30 m)[37, 38]. A fast walk is a guideline that mimics the speed of a fast walk through a junction. The status of altered cognitive function under the different intervention modalities was assessed by comparing oxygen saturation in the prefrontal cortex before and after the intervention, and by combining indicators such as step frequency, step speed and walking time during the period [39, 40]. In order to minimise experimenter-related methodological bias, the same assessor administered the same instructions to each subject. Each subject completed the task twice, once for familiarisation and once for assessment. Figure 4 shows the fNIRS instrument (portable NirSmart II-3000B Huitron Medical Devices Ltd.) that will be used in this study. It is possible to perform the relevant motor tasks in wireless transmission mode and record the cortical changes in oxyhaemoglobin during the performance of the task in continuous wave form. The light sources are fixed to the head cap at a distance of 30 mm, with a full channel sampling frequency of 11 Hz and wavelengths of 760 nm and 850 nm, respectively, with the detection area being the centre of each light detection point, and with specific brain area cues on the device to ensure accuracy of brain area monitoring.

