## Research methodology

### Design

This study was a single-centre randomised controlled study with three measurement periods (One week before the experiment, week 6 of the experiment and the first week after the experiment.). Assessors for cognitive and physical tests and data analysts are formally blinded, while participants and trainers are unblinded. Eighty-one COPD patients (GOLD I-II) will be recruited for this study and randomly assigned in a 1:1:1 ratio to the HG, BDJ and CG groups, with the HG and BDJ groups receiving a 12-week motor rehabilitation intervention. The availability of oxygen in the dorsolateral prefrontal cortex (PFC) was monitored by fNIRS at all times during the cognitive task, and cognitive function was assessed in conjunction with relevant cognitive scales. To explore the improvement of cognitive function in COPD patients by strong abdominal breathing in a head-down position. This study design and participant flow is shown in Fig. 1, and the relevant demographic and baseline data indicators to be measured are shown in Table 1. For the study duration and SPIRIT checklist, please see the Additional file.

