#### Cognitive behavioural ability is measured by the following indicators

The physical exertion index (PCI) is the difference between the heart rate during the walking task and the heart rate at rest divided by the walking speed. Subjects’ cognitive abilities were assessed by using the PCI index to reflect changes in their cognitive abilities during the motor cognitive task.Timed-Stand-Walk (TUGT) is a measure of balance and agility that requires the subject to sit in a chair, time starts, the subject stands, and walks 3 m, then turns 180 degrees to return to the chair and records the time taken.The gait test analysis equipment was used to assess the patient’s level of cognitive behavioural ability in terms of changes in step frequency, step speed and walking time before and after the intervention in a 30-m rapid step speed task.

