For the improvement of cognitive function in patients with COPD combined with MCI, We analysed data on the status of changes in oxyhaemoglobin in the prefrontal cortex of the brain during the task (walking) as detected by fNIRS. The fNIRS analysis only considered the single-task condition, as we expected confounding behavioural differences to occur in the dual-task condition, and therefore the fNIRS analysis was not valid in this condition [53]. However, fNIRS will inevitably generate noise and artefacts during the motion task [54–56], such as breathing, heartbeat, environmental noise and instrument noise, which will interfere with the reliability of the experimental data analysis [57], We will also correct the relevant data. However, in order to enhance the true reliability of the experimental results, we will also assess cognitive functioning more comprehensively with the internationally used Montreal Cognitive Assessment Scale (MoCA), the Revised Addenbrooke’s Cognitive Examination (2012) ACE-R and specific cognitive domains (i.e. attention (Attention Matrix Test), memory (Digital Breadth Test DST), executive ability (TMT Connectedness Test A-B), fluency (VFT)) and cognitive behavioural ability level tests.

In conclusion, this study will explore a new community-based PR programme for patients with COPD combined with IC in order to promote its application in the general population. The HG will be used to intervene in the cognitive function, mental status and motor ability of patients with COPD combined with MCI, and to select a proven intervention that will enrich the current PR programme for COPD.

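### The fNIRS primary outcome is said to be recorded in a cognitive task but is measured in plain walking; its quantity is not fixed, and a cognitive conclusion is drawn from it

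*Protocol article*

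**What the plan says.** The article has one outcome under Main results, the prefrontal tissue oxygen saturation index (TSI).

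- **Task.** The TSI section opens with "Monitoring changes in dorsolateral prefrontal cortex (PFC) oxyhemoglobin concentration by fNIRS at all times during a cognitive task", and the Design section states "The availability of oxygen in the dorsolateral prefrontal cortex (PFC) was monitored by fNIRS at all times during the cognitive task". The procedure later in the TSI section reads "For the measurement of the TSI, This study was designed to use a single-task walking test in two contexts". The two contexts are a usual-pace and a fast-pace walk. The Discussion equates the task with walking and adds "The fNIRS analysis only considered the single-task condition".
- **Quantity.** TSI "is calculated as the ratio of oxy-Hb to the percentage of Total-Hb". The opening sentence of the same section speaks of changes in oxyhaemoglobin, and the device is said to "record the cortical changes in oxyhaemoglobin during the performance of the task in continuous wave form". The Discussion again names change in oxyhaemoglobin as the analysed signal. The Statistical analysis section lists oxy-Hb, Deoxy-Hb, Total-Hb and TSI together and does not say which is primary.
- **Interpretation.** The TSI section describes TSI as a stand-in for tissue oxygenation, then says that altered cognitive function is assessed by comparing prefrontal oxygen saturation before and after the intervention, combined with gait indicators.
- **Related measures.** The cognitive behavioural section says that subjects' "cognitive abilities were assessed by using the PCI index to reflect changes in their cognitive abilities". Table 1 places the Berg Balance Scale under specific cognitive functions, and PCI, TUGT and three 30-m gait measures under cognitive behavioural assessment.

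**The concern.** The stated aim is to improve cognitive function, and the primary outcome carries the headline claim. If it is recorded in walking without cognitive load, it describes prefrontal oxygenation in walking. Two arms train three times a week for 12 weeks, while the control group has medication only. Training could alter heart rate, gait and cerebral haemodynamics during a walk with no change in cognition, and under the present wording such a difference would be reported as a cognitive gain.

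The unsettled quantity adds a second risk. Two candidate quantities (TSI, change in oxy-Hb) at two paces give 2 × 2 = 4 possible primary results, and the article does not choose among them. The Sample size section bases the trial's size on the key outcome indicators, so it matters which one is meant.

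**Working it through.** No sample-size or power figure bears on this point. The check compares the sections, with one small illustration and one count.

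**1. Task**

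| Section | Task during fNIRS recording |
|---|---|
| Design | cognitive task |
| TSI, opening sentence | cognitive task |
| TSI, measurement procedure | single-task walk, usual pace and fast pace |
| Discussion | walking; single-task condition only |

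Of the two recording conditions described, 0 include a cognitive component. All four statements are current text and cannot all be followed.

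**2. Quantity**

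Take TSI = 100 × oxy / (oxy + deoxy), which is the article's ratio expressed as a percentage. The levels below are assumptions in arbitrary units, since the article gives none. Oxy-Hb rises by 1 in every row.

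| Start (oxy/deoxy) | Change in deoxy | TSI after | Change in TSI (points) |
|---|---|---|---|
| 60/40 (TSI 60) | −0.3 | 61/100.7 = 60.58 | +0.58 |
| 60/40 | +0.667 | 61/101.667 = 60.00 | 0.00 |
| 60/40 | +1.5 | 61/102.5 = 59.51 | −0.49 |
| 30/20 (TSI 60) | −0.3 | 31/50.7 = 61.14 | +1.14 |
| 30/20 | +0.667 | 31/51.667 = 60.00 | 0.00 |
| 30/20 | +1.5 | 31/52.5 = 59.05 | −0.95 |

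An identical oxy-Hb change can accompany a rise, no change or a fall in TSI. The size also depends on the starting level: with the same changes, it is about twice as large at 30/20 as at 60/40. The two quantities are therefore not interchangeable as a primary outcome. The sizes are illustrative; the possibility of opposite signs follows from the ratio itself.

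**3. Inference**

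By the article's own account TSI reflects the balance of oxygen delivery and use. Nothing in the two walks scores a cognitive response. Moving from this measure to altered cognitive function is an added assumption, and it is weakest for HG or BDJ against the control group, where training itself differs. PCI shows the same step: by its formula it is (walking heart rate − resting heart rate) / walking speed, a cardiorespiratory cost.

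**4. Share of physical measures**

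Table 1 rows from MoCA down:
- Overall: MoCA, Stroop, ACE-R, MMSE = 4
- Specific: TMT-A, TMT-B, DST, VFT, Berg, elimination test = 6
- Behavioural: PCI, TUGT, pace, walking time, cadence = 5

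Total 4 + 6 + 5 = 15. Physical performance: Berg plus the 5 behavioural rows = 6 of 15 (40%).

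**The case against.** Four points can be made for the protocol.

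- **Single-task recording is deliberate.** The Discussion expects behavioural confounding under dual-task conditions and avoids it for that reason. The cognitive behavioural section also calls the walk a motor-cognitive task, so part of the conflict is loose terminology. The reason stands as a defence of recording during walking. It does not make walking a cognitive task or support a cognitive reading.
- **The instrument may well yield TSI.** A reader might infer from the continuous-wave wording that the device cannot produce the ratio. The documents do not establish this. The procedure is introduced as the measurement of TSI, two wavelengths are given, TSI is in the analysis list, and the phrase may only mean a continuous trace. What stands is that the outcome is described in two ways and neither is named as primary.
- **The trial does measure cognition.** A reader might infer that the trial as a whole cannot separate a fitness effect from a cognitive one. That goes too far. MoCA, ACE-R, MMSE, Stroop, TMT, digit span, verbal fluency and the elimination test are collected, and the Discussion says the cognitive tests are there to strengthen the fNIRS results. HG is also compared with BDJ, an active arm matched on session length, frequency and duration, which limits a general-exercise explanation without removing it. The criticism is confined to the primary outcome and its interpretation.
- **The class labels are secondary.** Berg, PCI, TUGT and gait are not the primary outcome, and relabelling them does not alter its analysis. That is true, but the labels invite the same misreading.

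**Conclusion.** The point holds for the primary outcome. Two places put the fNIRS recording in a cognitive task; the only procedure given, and the Discussion, put it in single-task walking. The outcome is defined as TSI and also described as change in oxyhaemoglobin, two quantities that can move in opposite directions, and pace is left open as well. A cognitive conclusion is then drawn from a measure that the article itself treats as reflecting tissue oxygenation.

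The conclusion rests on the text alone. The TSI figures use assumed levels and show only that size and sign can differ. It is not claimed that a haemodynamic effect without cognitive change will occur, only that the primary outcome as described would not distinguish it.

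**What to change.** 1. In the Design section and the opening of the TSI section, replace the cognitive task with single-task walking.
2. Name one primary quantity at one walking pace: TSI if the device yields oxy-Hb and Total-Hb levels comparable across visits, otherwise task-related change in oxy-Hb. Make and date this choice before results by group are seen, and report the other quantity and pace as secondary.
3. Limit the primary conclusion to prefrontal oxygenation during walking.
4. Rest the cognitive conclusion on one named scale already collected. MoCA is a reasonable choice, since entry is restricted to MMSE 23–27; note that scores below 17 on MoCA are excluded, so its range is cut from below.
5. Report Berg, PCI, TUGT and the three gait measures as physical function.

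The cost is wording in the protocol and registry, and a narrower claim for the fNIRS measure. No new data are needed. Adding fNIRS during the Stroop test might seem attractive, but with training from 1 February 2024 and completion expected by April 2024, the stated schedule no longer allows a baseline recording.

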## Discussion

This study will examine the improvement of cognitive function in patients with COPD combined with MCI in terms of physiological indicators and assessment scales. In the past, patients with cognitive impairment have been excluded from PR programmes for COPD patients due to their frequent memory loss, dysfunction, and poor physical and mental health, which hinder the effectiveness of PR interventions [8]. There is a need to explore treatments that can improve cognitive function in COPD patients in order to improve the quality of their survival [41]. Aras et al. [42] showed that the coexistence of sleep disturbance, depression and anxiety with COPD increased cognitive impairment and the severity of the disease. In a study on the relationship between cognitive function and the brain, Savage et al. [43] found in their study that frontal lobe atrophy was significantly greater in COPD patients than in controls (*p* = 0.02) using a visual rating scale, and that cognitive function was significantly worse in the COPD group in terms of executive function (*p* < 0.001), working memory (*p* = 0.02), verbal memory (*p* = 0.03) and processing speed (*p* = 0.001) were significantly worse. In a PR programme for a population of patients with COPD combined with cognitive impairment, Andrianopoulos et al. [44] compared cerebral oxygen availability during exercise in cognitively impaired (CI) and cognitively normal (CN) COPD patients. During exercise, CN and CI patients exhibited mild to moderate decreases in SpO2 (nadir [Δ] ≥  − 3 ± 2% and – 5 ± 3%, respectively) but maintained baseline frontal cortical TSI levels, while presenting small TcPCO2 perturbations and increased total brain-Hb (post [Δ] ≥ 2.0 ± 3 μM s − 1). Patients with CI retain the ability to adequately maintain cerebral oxygen availability during submaximal exercise. Therefore, rehabilitative exercise training for patients with COPD combined with CI who exhibit mild to moderate exercise-induced decreases in SpO2 does not appear to result in reduced cerebral oxygen availability. As in healthy older adults, cardiorespiratory fitness is positively associated with cognitive function in COPD patients [45], and cognitive function in COPD patients can be improved by targeted cardiorespiratory interventions in PR programmes.

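### Change in cognitive function is read from walking TSI, a measure the protocol describes only as tissue oxygenation and gives no direction of benefit

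*Protocol article*

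**What the plan says.** The section on TSI under Main results of the protocol article makes three statements that matter here.

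- **What TSI is.** It "reflects the balance between oxygen delivery and utilisation", and the section goes on to limit its meaning: "In the brain, TSI is used as a proxy for tissue oxygenation".
- **What happens in an activated region.** Within a task, "higher concentrations of oxyHb and reduced concentrations of deoxyHb are observed in the activated brain regions".
- **How TSI will be used.** Change in cognition in each arm is to be "assessed by comparing oxygen saturation in the prefrontal cortex before and after the intervention". Gait measures from the same walks enter this assessment too, "by combining indicators such as step frequency, step speed and walking time during the period". The recording is made during single-task walks of 30 m, at usual and at fast pace.

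The Discussion cites one study that measured TSI in COPD. Cognitively normal and cognitively impaired patients had mild to moderate falls in SpO2 during exercise, "but maintained baseline frontal cortical TSI levels". The article concludes: "Patients with CI retain the ability to adequately maintain cerebral oxygen availability during submaximal exercise". It uses this to argue that exercise training should not reduce the brain's oxygen supply in such patients.

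**The concern.** The main outcome is a physiological quantity, but the plan states that a change in it will be read as a change in cognition. Two things are needed for that reading: a reason to think TSI during walking tracks cognitive function in these patients, and a statement of which way TSI should move if the treatment works. The article gives neither.

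Without a declared direction, a rise can be described as better oxygenation and a fall as more economical activation, and both can be called improvement. The sentence in the TSI section would then turn an oxygenation result, whatever its sign, into a statement about cognitive benefit in patients with COPD and mild cognitive impairment.

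**Working it through.** The plan gives no figure on this point. The sample-size inputs (effect size 0.25, alpha 0.05, power 0.8, 69 patients raised to 81) say nothing about the direction of TSI. The check is therefore a comparison of sections.

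**Step 1. Does the definition of TSI imply a direction?** The article defines TSI from oxy-Hb relative to total Hb. Taking total Hb in its usual sense, TSI = oxy-Hb / (oxy-Hb + deoxy-Hb), as a percentage. On the article's own account this reflects supply against use:

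| Change after training | TSI | Possible account |
|---|---|---|
| Supply up, use unchanged | rises | better delivery |
| Supply unchanged, use down | rises | less neural demand |
| Supply down, use unchanged | falls | worse delivery |
| Supply unchanged, use up | falls | more neural demand |

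Each sign has two accounts, and the definition does not choose between them.

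**Step 2. Does the activation account supply a direction?** It describes the acute response within a task: oxy-Hb up, deoxy-Hb down. It does not say whether a patient who has benefited from 12 weeks of training should show more or less of that response in the same walk. The comparison planned is between visits, so the gap remains.

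**Step 3. Is a direction given for other measures?** Yes, for several. ACE-R, MMSE, verbal fluency and the Berg scale are each described as better when higher. The mMRC and SGRQ are described as worse when higher. MoCA has a normal cut-off (26 or more out of 30), which implies one. Some secondary tests, such as the trail-making test, have no stated direction either, but the omission matters most for the main outcome.

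**Step 4. Do the gait indicators close the gap?** Table 1 lists pace, walking time and cadence under cognitive behavioural assessment, so the protocol does regard them as related to cognition. The TSI section gives no rule for combining them with TSI. It does not say, for example, what follows if TSI falls while pace improves. Table 1 also places TSI itself outside all three of its cognitive blocks.

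**Step 5. Does the cited COPD evidence support the reading?** The Discussion reports that impaired and normal patients both kept TSI at their baseline during exercise. On that report, the exercise TSI response did not distinguish the two groups. The evidence is used to reassure about cerebral oxygen supply. It does not show that TSI during exercise indexes cognitive status.

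**The case against.** **Cognition is not judged on TSI alone.** The Introduction speaks of evaluating improvement from several perspectives, and the Discussion says cognitive scales are added to make the results more reliable. This stands, and it limits the point. It does not remove the sentence in the TSI section that reads cognitive change from TSI and gait without reference to any scale. Nor does the article say what is concluded if TSI and the scales disagree.

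**A favourable direction is implied.** The Introduction names hypoxaemia among the causes of cognitive impairment, TSI stands for oxygenation, and the Discussion treats reduced cerebral oxygen availability as unwanted. A reader would guess that higher is better. That is a fair inference, and nothing in the article announces an intention to present a fall as benefit. But it remains a guess about the main outcome.

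**Rules of interpretation may sit in a fuller protocol or analysis plan.** If the only gap were the missing direction, this would largely answer it. The article goes further: it states the inference from oxygenation to cognition, and that statement needs changing wherever the details are kept. The cited references may argue for the link, but they are not reproduced, so no judgement is made on whether TSI could ever index cognition.

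**A stronger reading is tempting.** One might infer from the Discussion that these patients have no TSI deficit to correct, and hence that a positive TSI result would probably be chance. The article does not support this. It reports only that TSI did not fall from each patient's own baseline during submaximal exercise. It gives no TSI level for either group, no comparison of levels, and nothing on the 30-m walk or on change over 12 weeks. Stability within a session does not show whether training shifts TSI between visits.

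**Conclusion.** The point holds in this form. The protocol assesses change in cognitive function from a before-and-after change in walking TSI plus gait indicators, with no rule for combining them. It describes TSI only as an oxygenation proxy, and it declares no favourable direction. The COPD evidence it reports shows no exercise-induced fall in TSI in impaired or normal patients, so that response did not separate them. A change either way could be presented as cognitive improvement.

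The size of the problem cannot usefully be put as a number. Power calculations for small TSI effects would need assumed effect sizes and would not bear on direction. What is affected is the conclusion the trial may draw from its main outcome. The verdict rests on the article's text alone and assumes that no fuller document, not shown, replaces the sentence in question. It is a matter that should be corrected; it does not invalidate the trial, because the cognitive scales needed for a sound claim are already being collected.

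**What to change.** In the TSI section under Main results:

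1. Replace the sentence that assesses cognitive function from TSI. State instead that TSI is reported as prefrontal oxygenation during walking, a physiological outcome.
2. State which direction of TSI change is favourable and why, before the data are analysed. Report a change in the opposite direction as unfavourable. If outcome data by group have already been examined, say so and label the choice post hoc.
3. State that cognitive improvement is claimed only from a between-group difference on one prespecified cognitive scale already collected. MoCA is one candidate; the choice is the investigators' to make and justify. Apply the same rule to HG and to BDJ.

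No new measurement or visit is needed. The change does narrow what the trial can say: a TSI result alone can no longer be presented as cognitive improvement.
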